## Abstract

Introduction: Responsive caregiving is one of the most fundamental pillars of early childhood development. In the newborn stage, the parents are undergoing transitions and require support to understand the nuances of interacting with the young baby. The role of healthcare facilities in this becomes vital as a hub for conducting parenting education sessions that may yield thriving outcomes for young children and their future development. This study aims to explore the impact of the early childhood newborn parenting program on parental confidence and newborn responsive interaction and to explore the perceptions of healthcare providers regarding the intervention implemented in healthcare settings.

Methods: An implementation research design will be used in this study. A total of 500 participants will be included in the study, 400 from Pakistan and 100 from Afghanistan. There are two sites: each site will be randomly assigned as a control or an intervention. The rationale was to ensure that both sites are in different geographical locations. Participants from each side will be chosen using a convenience sampling technique. Cohort 1 (control group) will only be provided with a self-study, one consolidated handout on responsive caregiving, and one-time bed teaching, and will be requested to visit the center after six months (child age) for an endline. While cohort 2 (intervention group) will be provided a six-module intervention consisting of one session at birth with a self-study handout on responsive caregiving, and five monthly sessions (once a month till the infant turns six months) will be conducted. Outcomes measured at the baseline and endline (at six months) include differences in responsive interactions and parenting confidence scores between the control and intervention groups using tools such as Karitine parenting confidence, responsive interaction scale, Caregiver Reported Early Development Instruments (CREDI), WHO QoL, and Patient Health Questionnaire (PHQ).

Results: This is an ongoing study protocol, and the analysis of the results is expected in December 2025.

Discussion: The study will be one of its kind to have been implemented from a healthcare setting, whereby the formal newborn responsive parenting intervention is used, particularly in remote areas of Pakistan and Afghanistan, using a primary healthcare facility for implementation. The study will establish the feasibility of a novel intervention and provide a model of utilization of healthcare settings as hubs for early childhood (ECD)-responsive parenting education. Evidence from this study will be largely applicable to countries with limited resources and countries that are striving to make early childhood parenting education more accessible to the communities.

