## Materials and methods

Study design

This before-and-after implementation feasibility study will examine the feasibility, fidelity, and adaptation of this intervention in the primary healthcare settings of remote Pakistan and Afghanistan. Implementation research is a relatively new approach in the medical sciences, but it has been widely used in various global, public health, and social sciences research. It also has great potential to allow flexibility for the researchers to be engaged and involved in the process of research. The field sites will be conveniently divided into two groups. The intervention and the control. The intervention group will undergo a structured responsive parenting education program, i.e., six sessions in the first five months of life on a structured curriculum under the supervision of trained lady healthcare workers, while the control group will undergo limited intervention, i.e., a compiled handout at birth for self-study (outlined in Figure 1). 

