**Figure 1 FIG1:**
[figure not shown]
Flow chart of the study procedure

Study setting

Participants will be recruited from the six basic health centers (BHCs) of not-for-profit private healthcare systems in Pakistan and Afghanistan. These BHCs will be chosen as primary healthcare facilities to pilot the intervention, as shown in Tables 1-2. The BHCs provide maternal, newborn, and child health services (MNCHS), including antenatal care, delivery, and postnatal care (ANC-PNC), family planning, immunization, adult health screening, and regular growth monitoring of <3 years old. Through lady health visitors (LHVs), responsive parenting education will be integrated into their maternal and newborn care model.

**Table 1 TAB1:** Field sites (Pakistan) F4HE: Foundations for Health and Empowerment

S/n	Site Selection	Location of Health Facility	Type of Health Facility	Level of Services	Average Deliveries Per Month	Covering Under F4HE Geographical Areas
1	Pakistan Intervention Group Site 1 (PIGS 1)	District Upper Chitral	Basic Health Center	Primary	10	Yes
							Pakistan Intervention Group Site 2 (PIGS 2)	District Lower Chitral	Basic Health Center	Primary	4	Yes
	2	Pakistan Control Group Site 1 (PCGS 1)	District Upper Chitral	Basic Health Center	Primary	10							Yes
							Pakistan Control Group Site 2 (PCGS 2)	District Lower Chitral	Basic Health Center	Primary	4	Yes	

**Table 2 TAB2:** Field sites (Afghanistan) F4HE: Foundations for Health and Empowerment

S/n	Site Selection	Location of Health Facility	Type of Health Facility	Level of Services	Average Deliveries per Month	Covering Under F4HE Geographical Areas
							1	Afghanistan Intervention Group Site 1 (AIGS 1)	Baharak District	District Hospital (DH)	Primary and Secondary	265	Yes
							2	Afghanistan Control Group Site 1 (ACGS 1)	Jurm District	Comprehensive Health Center (CHC)	Primary	77	No

Eligibility criteria

Inclusion criteria for the study enrolment are (i) the newborn’s mother following a normal delivery; (ii) the newborn does not exhibit any underlying morbidities; (iii) the family is not living in ultra-poverty with less than 15,000/- total household income; and (iv) the family can understand Urdu. The exclusion criteria for the study include (i) newborns with underlying conditions or morbidities, (ii) the family living on a 15,000 household income per month, and (iii) mothers with postpartum depression.

Study intervention

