A total of 500 participants will be chosen, 100 from four primary healthcare facilities in the regions of Chitral, Pakistan, and 100 from two primary healthcare facilities in Afghanistan. A total of 200 before-intervention participants as a control group and 200 intervention participants in Pakistan will be recruited. Similarly, for Afghanistan, 50 pre-intervention (control) participants and 50 intervention participants will be recruited as a control group. The sample size is chosen based on convenience sampling, and the facilities are selected considering the number of deliveries and outreach feasibility. It is anticipated that 40% of the total annual deliveries may consent to participate, and based on calculations, this will help us achieve our N for each of the cohorts. Additionally, there might be variations in the actual data collection.

Data collection plan

We will have two cohorts: a cohort before the intervention and an after-cohort with the intervention. Each cohort will last for six months.

Cohort 1 (control group): Baseline data will be collected, and they will be provided with a self-study pictorial module. They will be tracked and requested to visit the center at six months (child age) post-delivery. At six months, their endline data on responsive interactions, parenting confidence, and patient experience will be collected.

Cohort 2 (intervention group): Baseline data will be collected, and they will be provided a six-month intervention consisting of one session at birth with a self-study manual, and five monthly sessions (once a month till the infant turns six months). At six months, they will also be assessed on the measures mentioned above, and endline will be collected.

Data analysis

Both qualitative and quantitative data analysis strategies will be used to conduct data analysis.

Quantitative analysis will be performed using the statistical package for the social sciences (SPSS Inc., Chicago, IL). Descriptive statistics, such as frequencies, percentages, means, and SD, will be computed for demographic characteristics, QoL, and parental outcomes (confidence, feeding, and teaching assessment using KPSC, NBRI score). Independent sample t-test, paired test, and repeated measure ANOVA will be used to compare within and between-subject effects. Multilevel logistic regression will also be performed for categorical outcomes to observe the effectiveness after controlling for the confounding factors. P≤0.05 will be considered significant.

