## Conclusions

This protocol aims to conduct a before-and after (quasi-experimental design for this arm of the study) and implement a newborn parenting education program in primary and secondary healthcare settings in low- and middle-income countries such as Pakistan and Afghanistan, where early childhood development and responsive parenting education in healthcare settings are least prioritized. The findings of this study, through its data, will inform policy makers and other key stakeholders in understanding the significance and nuances of integrating the early childhood responsive parenting education program in the existing maternal and child health system, particularly in primary and secondary healthcare settings.

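### The protocol describes its comparison in incompatible ways: random or convenience allocation of sites, and separate control facilities or a before-cohort and an after-cohort

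*Protocol article*

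**What the plan says.** **Allocation.** The abstract states: "There are two sites: each site will be randomly assigned as a control or an intervention". Study design states: "The field sites will be conveniently divided into two groups". The limitations section recommends a randomised trial as later work, and the Conclusions describe the present study as "before-and after (quasi-experimental design for this arm of the study".

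**Comparator.** Study setting says "Participants will be recruited from the six basic health centers (BHCs", and Tables 1 and 2 list the facilities by arm: two intervention and two control facilities in Chitral, and one of each in Afghanistan. Study design opens with "This before-and-after implementation feasibility study will examine the feasibility, fidelity, and adaptation of this intervention". The Data collection plan says "We will have two cohorts: a cohort before the intervention and an after-cohort with the intervention". The sample size section likewise labels the control mothers in both countries as recruited ahead of the intervention.

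**Control package.** The abstract gives control mothers a handout and "one-time bed teaching". Study design describes a "limited intervention, i.e., a compiled handout at birth for self-study". The Data collection plan mentions only a pictorial self-study module.

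**The concern.** A comparison of randomised sites, a comparison of non-randomised sites over the same period, and a comparison with an earlier cohort support different conclusions. The protocol has wording for all three, and its abstract claims the strongest.

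The feasibility label does not make this harmless. The first research objective compares the intervention group with a cohort that did not receive the intervention, and the Discussion expects the results to bear on potential effectiveness and on guidelines.

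Confounding by site or period is not acknowledged anywhere. The limitations section treats convenience sampling as a question of generalisability only. It mentions regime change and climate crises only as threats to reaching the target sample. If the cohorts are sequential, those same events can also differ between the arms.

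**Working it through.** **1. Allocation statements side by side**

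- Abstract: random assignment of sites.
- Study design: division of sites by convenience.
- Limitations: a randomised trial is left for later.
- Conclusions: quasi-experimental.

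The first cannot stand with the other three. No section describes a draw.

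**2. Comparator statements side by side**

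- Tables 1 and 2: control mothers come from different facilities from intervention mothers.
- Sample size section and Data collection plan: control mothers come from before the intervention, intervention mothers from after it.

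Here before and after cannot mean baseline and endline, because the Data collection plan applies the words to the two cohorts, and each cohort has its own baseline and six-month assessment. Three readings remain:

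| Reading | Arm confounded with |
|---|---|
| Separate facilities, same calendar period | facility |
| Same facilities, successive periods | period |
| Separate facilities, successive periods | both |

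**3. Does the planned sample size show which reading is meant?**

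Inputs: deliveries per month in Table 1 (10 + 4 = 14 per arm, 28 over all four Chitral facilities), 40% consent, and 200 per Pakistan cohort.

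The total reproduces: 200 + 200 + 50 + 50 = 500. The 200 does not:

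- Separate facilities: 14 × 12 × 0.40 = 67 per arm per year; 200 / (14 × 0.40) = about 36 months.
- All four facilities in turn: 28 × 12 × 0.40 = 134 per cohort per year; 200 / (28 × 0.40) = about 18 months.

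Afghanistan's 50 is reachable either way (77 × 12 × 0.40 = 370 a year at the smaller facility). The sample size therefore does not settle the design. The accrual shortfall is a separate matter.

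**4. Facility and arm in Afghanistan (Table 2)**

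- Intervention: one District Hospital, primary and secondary care, 265 deliveries a month, inside the F4HE area.
- Control: one Comprehensive Health Center, primary care, 77 deliveries a month, outside it.

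With one facility per arm, facility and intervention are the same variable. In Chitral the facilities are matched on district and volume (10 v 10 and 4 v 4), which helps but leaves two per arm.

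**5. Illustration of size (assumed inputs; the documents give none)**

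*Facility.* Assumed intracluster correlation (ICC) of 0.01 to 0.10, and an individual-level two-sided t-test of endline scores at 0.05. Design effect = 1 + (m − 1) × ICC, where m is the number of mothers per facility; true type I error = 2 × [1 − Φ(1.96 / √design effect)]. For Afghanistan, m = 50:

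- ICC 0.01: design effect 1.49, type I error 0.11.
- ICC 0.10: design effect 5.90, type I error 0.42.

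*Period.* Assumed shift of d SD between cohorts in the score analysed, n = 250 per arm, no true effect. False-positive rate = Φ(z − 1.96) + Φ(−z − 1.96), with z = d / √(2/250):

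- d = 0.1: z = 1.12, rate 0.20.
- d = 0.2: z = 2.24, rate 0.61.
- d = 0.3: z = 3.35, rate 0.92.

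**The case against.** The best defence is that the randomisation claim is one sentence in the abstract, and that the limitations and Conclusions show that the authors do not regard the study as a randomised trial. That makes the correction easy. It does not remove the error, since the abstract is the part most often read alone, and it does not touch the conflict over the comparator.

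Second, both cohorts are measured at baseline and six months, and repeated-measures ANOVA is planned. This has force. Comparing change removes stable differences in level between facilities, so the facility illustration applies to the endline t-test rather than to that analysis. It would therefore be wrong to infer that no adjustment can help. What change scores cannot remove is a shock that falls on one period only, or a different course over six months at one facility.

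Several stronger readings are tempting but unsupported:

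- *Arm wholly aliased with season.* This takes the six months per cohort as a window for births. It may equally mean follow-up of each child. In Chitral a six-month window could not supply 200 mothers even with full consent: 14 × 6 = 84, or 28 × 6 = 168.
- *Control mothers come from other facilities and an earlier period.* This merges two descriptions. No section states the combination.
- *Control sites deliver different packages.* The difference is between sections of the article; no section reports variation between sites. Nor is the bedside teaching equated with the intervention group's birth session.
- *Two sites contradicts six facilities.* The Introduction uses two sites for the two countries, so the count is ambiguous rather than plainly wrong.

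**Conclusion.** The concern stands as a contradiction in the current text on two matters: how sites were allocated, and whether control is defined by facility or by time. It is not a matter of detail left to a fuller document, because the statements conflict. As written, the abstract claims randomisation that the rest of the protocol does not support, and the reader cannot tell which comparison will be made.

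Confounding of arm with facility is certain in Afghanistan if Table 2 describes the comparison. Confounding with period, or with both, is possible and depends on calendar dates that the protocol does not give. The same-period reading is itself an inference from the separately named control facilities.

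The size of any bias cannot be derived from the documents. The error rates above rest on assumed ICCs and period shifts, on full enrolment and on a two-sided test, and show only that modest values would matter. The control package is a smaller point: its descriptions differ and must be reconciled.

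**What to change.** The study is already in progress, so the text should follow what was actually done.

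1. Delete the random-assignment claim from the abstract unless a documented draw took place, and call the study a non-randomised controlled (quasi-experimental) study throughout. If there was a draw, describe it and correct Study design. A draw within the two Chitral pairs would not undo the choice of facilities by convenience, nor separate facility from arm in Afghanistan.
2. State one comparator everywhere, naming the facilities and the calendar window that supply each cohort.
3. If enrolment is still open, recruit control and intervention mothers over the same calendar window in each facility pair, and remove the before/after cohort wording. If the cohorts were in fact sequential, keep that wording, state the dates, and limit the effect claims to match.
4. Present the Afghan result as a contrast in which facility and intervention cannot be separated.
5. Reconcile the abstract's control package with those in Study design and the Data collection plan.

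**Cost.** Mostly wording. Aligning the recruitment windows costs more and may no longer be possible. The randomised label is lost and the causal claims become weaker.

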There are possible limitations of this study. A convenience sampling technique will be used, which might lead to low generalizability and underrepresentation of the targeted population. The reason for using this sampling technique because it depends on the volume of deliveries in healthcare facilities in both regions. This seems to be best suited within the context of adaptation and exploring the implementation impact. However, a randomized controlled trial is recommended in the future to see the results of the intervention on a large scale. Challenges we might face due to having two different geographical settings. One geographical setting has a post-crisis conflict recovery and changes of regime in the region. In the second setting, where climate crises are happening, that might limit to achievement of the target sample size.

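### Mothers are chosen by convenience at facilities whose arm is already known, so selection can differ between arms, with most room for it in Afghanistan; the limitations mention only generalizability

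*Protocol article*

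**What the plan says.** **Allocation.** The Abstract says that "each site will be randomly assigned as a control or an intervention". Study design says: "The field sites will be conveniently divided into two groups". These two statements need reconciling, but under either one the arm belongs to the facility and is fixed before any mother is approached. Tables 1 and 2 already name every facility by its arm.

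**Choice of mothers.** "Participants from each side will be chosen using a convenience sampling technique" (Abstract). The sample size section and the limitations also name convenience sampling.

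**What each arm asks.** Intervention mothers have a session at birth and five monthly sessions. Control mothers receive self-study material and are asked to come back once, at six months (Abstract; Data collection plan).

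**Volumes and targets.** Table 1, under "Average Deliveries Per Month", gives 10 and 4 for each Pakistani arm. Table 2 gives 265 for the Afghan intervention hospital and 77 for the Afghan control centre. Targets per arm are 200 in Pakistan and 50 in Afghanistan. The sample size section expects 40% of annual deliveries to consent and says that this suffices for each cohort.

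**Stated limitation.** Under Plausible limitations and risk mitigation, convenience sampling is described as something "which might lead to low generalizability and underrepresentation of the targeted population". The reason given for using it is its dependence on delivery volume.

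**The concern.** The limitation as written concerns external validity. The first research objective, however, is a comparison of the intervention group with a group that does not receive the intervention, so what matters most is whether the two groups were assembled in the same way.

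A recruiter with free choice, who knows that one arm requires six attendances and the other a single return visit, has a reason to approach different mothers in each. Willingness to attend, education and distance from the facility are plausible grounds, and each may be related to parenting confidence and responsive interaction. Any such difference would enter the between-arm contrast and could create an apparent effect or hide a real one.

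The planned analysis offers limited protection. Data analysis states control of confounding only for categorical outcomes, by multilevel logistic regression. The t-tests and repeated measures ANOVA for the scores name no covariates.

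**Working it through.** **1. The plan's own figure.** Expected consenters per year = 0.40 × monthly deliveries × 12.

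| Arm | Monthly deliveries | Consenters per year | Target |
|---|---|---|---|
| Afghanistan, intervention | 265 | 1,272 | 50 |
| Afghanistan, control | 77 | 369.6 | 50 |
| Pakistan, each arm | 10 + 4 = 14 | 67.2 | 200 |

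The assurance that 40% suffices holds for Afghanistan, with about 25-fold (1,272/50) and 7-fold (369.6/50) surpluses. It does not reproduce for Pakistan, where 200 exceeds even all 168 annual deliveries per arm (14 × 12). Room to choose is therefore an Afghan matter; in Chitral nearly every mother would have to be approached.

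**2. Share of Afghan deliveries needed.** Share = 50 / (monthly deliveries × months).

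| Enrolment window | Intervention | Control |
|---|---|---|
| 6 months | 50/1,590 = 3.1% | 50/462 = 10.8% |
| 12 months | 50/3,180 = 1.6% | 50/924 = 5.4% |

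The six-month window is an assumption. The Data collection plan gives six months as the length of a cohort, which may mean follow-up rather than enrolment. The twelve-month row uses the annual basis of the 40% figure. In any common window the control share is 265/77 = 3.4 times the intervention share.

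The denominators count all deliveries. Eligibility rules on delivery type, newborn health, income, language and maternal depression reduce the pool by an amount the article does not give. If a fraction f of deliveries is both eligible and willing, the six-month shares are divided by f:

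- f = 0.4: 7.9% and 27.1%
- f = 0.2: 15.7% and 54.1%

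**3. What a shift would do.** The article gives no SD, effect size or power, so the shift b between arms is assumed to be 0.2 to 0.3 SD.

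- *Afghan endline comparison, unadjusted:* the bias equals b, 0.2 to 0.3 SD.
- *Pooled comparison, only Afghan selection shifted:* Afghan weight = 50/250 = 0.20, so the bias is 0.20 × 0.2 = 0.04 to 0.20 × 0.3 = 0.06 SD. The article does not say whether countries are pooled.

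**4. Consequence for an Afghan test.** For a two-sided z-test at 0.05 with 50 per arm, SE = √(2/50) = 0.20 SD. This treats mothers as independent and ignores facility clustering.

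- *No true effect:* rejection probability = Φ(b/SE − 1.96) + Φ(−b/SE − 1.96). This is 5% at b = 0, 17% at b = 0.2 and 32% at b = 0.3.
- *Assumed true effect of 0.4 SD, opposing shift:* power = Φ((0.4 − b)/SE − 1.96). This is 52% at b = 0, 17% at b = 0.2 and 7% at b = 0.3.

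**5. Is consecutive invitation feasible?** Months to fill 50 places at 40% consent are 50/(0.4 × 265) = 0.5 and 50/(0.4 × 77) = 1.6, if all deliveries were eligible. Delivery volume does not stand in the way at either Afghan facility.

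**The case against.** **A small share is not bias.** Fifty consecutive mothers would also be 3.1% of 1,590. This is right. The shares show room to select, not that selection differs. A reader might infer that staff will pick mothers likely to attend six sessions; the article does not say who recruits or how, so that remains a possibility only.

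**The percentages rest on assumptions.** This also stands. Neither the six-month window nor the eligible share is given. Taken literally, the requirement that families understand Urdu could shrink the Afghan pool considerably.

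**The bias could be small.** A reader might infer that the study's main comparison would be off by 0.2 to 0.3 SD. The documents do not support that: the figure is assumed and applies only to unadjusted Afghan endline scores. Baseline scores are collected in both cohorts, and a stable shift in level cancels in the group-by-time contrast of a repeated measures analysis. Education and socio-economic status are recorded too, so it would be wrong to say that adjustment cannot help. It cannot remove selection on unmeasured motivation or on expected progress, and an independent t-test at endline removes nothing.

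**The authors are open about the design.** They call it a quasi-experimental feasibility study, admit convenience sampling and recommend a randomized trial. Procedural detail such as a screening log may sit in a fuller protocol, so its absence is not held against the article. What remains is a rule the article does state, with only one of its two consequences acknowledged.

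**Conclusion.** The point holds as a risk to internal validity that the plan creates and does not name. It follows from three stated facts: the arm is fixed by facility, mothers are then chosen by convenience, and the arms make different demands on them.

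The room for selection is wide and unequal in Afghanistan and small in Chitral. Its size there (3.1% against 10.8% of deliveries, or 1.6% against 5.4%) depends on the enrolment window and on an unknown eligible share, although the 3.4-fold ratio between all-delivery shares does not depend on the window. The bias itself cannot be estimated from the documents. Under an assumed shift of 0.2 to 0.3 SD it is that large in an unadjusted Afghan endline comparison and about 0.04 to 0.06 SD in a pooled one, with part removable by baseline adjustment.

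This should be changed, because a better rule costs little. A reader should not conclude that the results are already known to be biased, or that a better invitation rule would by itself make the Afghan arms comparable.

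**What to change.** - **Invitation rule.** Replace convenience sampling with the same consecutive rule in both arms: from a fixed start date at each facility, invite every eligible delivery until the target is met. At the two Afghan facilities, a fixed every-k-th eligible delivery would also serve and would spread enrolment over the window.
- **Log.** At each facility record deliveries, eligible, invited, consented and refused, and report the counts by arm.
- **If enrolment has advanced.** The article describes the study as in progress. In that case apply the rule to the remaining enrolment and reconstruct the log from delivery records.
- **Limitations.** Add that convenience choice at facilities of known arm may produce between-arm selection. State also that the new rule limits selection by staff only. It does not remove self-selection at consent, where about 60% are expected not to take part (100% − 40%), or the confounding of arm with facility in Afghanistan, where a district hospital is compared with a comprehensive health center.

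The cost is modest record-keeping at six facilities and a few changed sentences. The sample size targets do not change.
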